#### Study procedures

Routine retesting in established puberty is routine clinical practice in all trial sites. Children with GHD persistence at retesting will restart GH; those with GHD reversal will be offered study participation. Following consent, participants will be randomised to GH + (25–35 µg/kg/day) and GH − groups and followed in routine endocrine clinics until ‘Near FH’ (growth rate < 2 cm/year) is reached. In the GH − group, any unexpected decrease in IGF-1 concentrations below − 2 SD (lower limit of normal) at 6 months would trigger a repeat GH stimulation test and recommencement of GH if deficient.

The baseline visit for all patients will include confirmation of inclusion and exclusion criteria, informed consent/assent, randomisation and allocation of trial number, prescription of growth hormone (if randomised to continue treatment), a record of the preparation and dose prescribed, a record of concomitant medication and relevant medical history. Height, weight and Tanner stage will also be measured at baseline. All patients will have 6-monthly visits to measure height, weight, Tanner stage, serum IGF-1 (at 6 months and annually thereafter) as well as checking compliance with GH therapy and any concomitant medication and adverse event reporting. HRQoL will be measured using the CHU9D questionnaire at baseline and at each 6-monthly visit. A left hand X-ray will be conducted at enrolment and near FH, for central analysis using the BoneXpert software. Fasting lipids will be measured at baseline and near FH.

At near FH, all subjects will have a GH stimulation test to reconfirm GH status. Given the usual duration of pubertal growth until near FH is achieved, we have allowed for 3 years follow-up.

The information captured at the randomisation and subsequent visits are shown in Fig. 2.

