#### Planned interventions

Participants in the control arm (GH +) will resume receiving their GH treatment at a dosing level determined by their clinical care team (following the minimum 6-week discontinuation period required prior to randomisation). Participants in the experimental arm (GH −) will not resume GH treatment. Both arms will be followed up at 6 monthly intervals until near FH or the 36-month follow-up (whichever is soonest).

All currently available GH treatment preparations with the active ingredient Somatropin are allowed, as detailed in the British National Formulary for Children (BNFc) in the UK and Kindermedika in Austria (https://kindermedika.at/monographie/10222/somatropin).

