#### Sample size and power calculation

Determination of non-inferiority margin was carefully considered, following extensive consultation. A questionnaire was sent to all investigators, British Society for Paediatric Endocrinology and Diabetes clinical study group members, and a patient support group representative (*n* = 34), giving several options for ‘acceptable deficit’ in various FH outcomes. These FH outcome options for comparison between the GH + and GH − groups were (1) the percentage of children reaching normal adult height (0 ± 2SD), (2) the percentage of children reaching mid-parental TH (0 ± 2SD) and (3) the near FH (in SDS/cm). Near-FH standard deviation score (near FH-SDS) was selected as the primary outcome.

Whilst the percentage of children reaching mid-parental TH [26] was the most popular outcome amongst respondents, data were not available to inform a sample size calculation. However, all the above options to express FH will be analysed in this trial as secondary outcomes. Other secondary outcomes are HRQoL, lipid profile, cost-effectiveness, and the bone health index (assessing effect of GH + /GH − on bone accrual and bone age using BoneXpert software).

For the primary outcome measure of near FH-SDS with a non-inferiority design comparing means and assuming equal variance, a non-inferiority margin of 0.55 near FH-SDS, a one-sided test with alpha = 0.025 and 90% power, a group size of 57 (total *n* = 114) would be needed (calculated using the SSI procedure in Stata 13). This calculation was based on a near FH-SDS (SD) of − 1.6 (0.9) using data from a population-based registry for patients with idiopathic GHD treated with GH and completing the scheduled treatment [27]. The non-inferiority margin is based on clinical opinion. Additional observational studies gave consistent results. Using the LMS growth software, a 0.55 height SDS score (using British 1990 Growth Charts [28]) approximates to 3.8 cm for boys and 3.3 cm for girls at age 23. With 17% allowance for withdrawal and loss to follow-up, a total sample size of 138 is required.

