### Missing data and sensitivity analyses

Every attempt will be made to collect full follow-up data on all trial participants; it is thus anticipated that missing data will be minimal. Participants with missing primary outcome data will not be included in the primary analysis in the first instance. This presents a risk of bias, and sensitivity analyses will be undertaken to assess the effect of any missing data. In brief, this will include a multiple imputation approach, using important variables to predict the near FH SDS and a last observation carried forward (LOCF) approach, which assumes no change from the previous assessment.

A further sensitivity analysis will be conducted to assess the impact of participants who have not reached near FH by the end of the study. For the primary analysis, all participants will be included and for any participants who have not reached near FH, their height recorded at the end of study follow-up visit will be used. Although we anticipate this to be a rare event, we will conduct a sensitivity analysis (for the primary outcome only) which excludes any participants who have not reached near FH by the end of the study. Full details are included in the SAP.

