### Planned final analyses

The primary analysis for the trial will occur once all participants have either fulfilled the near FH definition (growth rate of < 2 cm/year and have reached a bone age of 14 years (females) or 16 years (males)), have completed the 36-month assessment or have withdrawn from the study or been lost to follow-up and corresponding outcome data have been entered onto the trial database and validated as being ready for analysis. All other outcome measure analyses will be undertaken when the final participant (as defined above) reaches their 36-month assessment.

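### The second hand X-ray and fasting lipids are tied to near final height only, so a child who finishes at 36 months without reaching it has no defined bone or lipid follow-up value in the text shown

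*Protocol article*

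**What the plan says.** - **Timing of assessments (Study procedures).** "A left hand X-ray will be conducted at enrolment and near FH, for central analysis using the BoneXpert software. Fasting lipids will be measured at"… For lipids, the two visits named are baseline and near FH. The final stimulation test is also placed at near FH. Serum IGF-1 is drawn at 6 months and yearly as well.
- **Outcome definitions (Secondary outcomes).** Bone age delay, bone age acceleration since enrolment and bone health index are all defined by near final height. Lipids and peak GH are defined at final height.
- **End of follow-up (Planned interventions).** Both arms are followed "until near FH or the 36-month follow-up (whichever is soonest"). Planned final analyses likewise counts a child as finished on completing the 36-month assessment. The Fig. 2 legend says that follow-up may run beyond 3 years for children not yet at near FH.
- **Definition of near FH.** Study procedures uses growth below 2 cm a year alone. Planned final analyses adds that the child must "have reached a bone age of 14 years (females) or 16 years (males"). The Fig. 2 legend also adds bone age, with the two ages attached to the opposite sexes.
- **Children not at near FH (Missing data and sensitivity analyses).** In the primary analysis, "for any participants who have not reached near FH, their height recorded at the end of study follow-up visit will be used". The related sensitivity analysis is limited to the primary outcome, and such children are expected to be rare.
- **Analysis sets (Secondary outcome measures).** Bone outcomes are non-inferiority outcomes, analysed like the primary by ITT and per protocol. Biochemistry outcomes are superiority outcomes, analysed by ITT.

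**The concern.** The plan foresees children who end the study without reaching near FH and gives them a height. It gives them no X-ray or lipid value, because those measurements and the outcomes built on them are attached to an event that these children have not had.

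Reaching near FH within 36 months depends on growth rate and, under two of the three definitions, on bone age. Both are post-randomisation quantities that continuing or stopping GH may change. A comparison restricted to children who reached near FH is therefore not a comparison of the groups as randomised, even if labelled ITT. An X-ray or fasting sample that was never taken cannot be recovered at analysis, so this needs settling in the schedule and outcome definitions.

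**Working it through.** **1. The plan's own sample size.** Inputs from Sample size and power calculation: "a non-inferiority margin of 0.55 near FH-SDS"; "a one-sided test with alpha = 0.025 and 90% power, a group size of 57"; mean (SD) of minus "1.6 (0.9) using data from a population-based registry".

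n per arm = 2 × SD² × (z₀.₉₇₅ + z₀.₉₀)² / margin² = 2 × 0.81 × (1.960 + 1.282)² / 0.3025 = 56.3, rounded up to 57, so 114 in total. A noncentral-t check at 57 per arm gives power 0.899. For loss: 114 / (1 − 0.17) = 137.3, rounded up to 138, matching "With 17% allowance for withdrawal and loss to follow-up, a total sample size of 138 is required". The figures reproduce and this point does not alter them. The 17% covers withdrawal and loss to follow-up and does not mention children who stay in but miss near FH.

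**2. Two children followed through the text.**

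| Child at 36 months | Closes at 36 months (Planned interventions) | Continues (Fig. 2 legend) |
|---|---|---|
| Still growing at 2 cm a year or more | Height used; no X-ray or lipid value defined | Measured later, at near FH |
| Growth below 2 cm a year, bone age under the threshold | Measured under Study procedures; not at near FH under Planned final analyses, so no value defined | Measured under either definition, but at different times |

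Whether a value exists therefore depends on which sections are followed. In addition, Planned final analyses sets the analysis of all other outcomes at the last participant's 36-month assessment, so longer follow-up would not necessarily be used.

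**3. How many children.** The documents give no rate. Over an assumed share f of 114 evaluable children:

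| f (assumed) | Without a value, 114f | With a value, 114(1 − f) | SE ratio, 1/√(1 − f) |
|---|---|---|---|
| 5% | 6 | 108 | 1.03 |
| 10% | 11 | 103 | 1.05 |
| 20% | 23 | 91 | 1.12 |

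The loss of precision is small. The issue is selection.

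**4. Can a direction be derived?** The threshold is an absolute bone age. The outcome is delay, taken here as chronological age minus bone age (an assumption). Inclusion criteria admit girls aged 8 to 15.

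- A girl enrolled at 8 is 11 at 36 months. With bone age 12 her delay is 11 − 12 = −1 year, so she is not delayed, yet she is below 14 and has no value.
- A girl enrolled at 15 and seen at 16 with bone age 14 has a delay of 16 − 14 = 2 years, yet she passes the bone-age condition.

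So the threshold does not sort children by delay.

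For absolute bone age alone, a simple model can be run: normal with SD 1, observed only above a cut-off c, mean among those observed = μ + φ(c − μ)/(1 − Φ(c − μ)). Assume a true shift of −0.5 SD in GH−. If 5%, 10% or 20% of GH+ children fall below c, the observed difference is −0.37, −0.32 or −0.26 SD, an attenuation of 26%, 36% or 49%. With no true shift the model shows no bias. The rates and the shift are assumed, and the model covers neither delay, bone health index nor lipids.

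**The case against.** Much of the case on the other side stands.

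- **The schedule is not visible.** Fig. 2 could contain an end-of-study X-ray or blood sample, and the article condenses a fuller protocol. This limits the claim to the text shown. Even so, a 36-month film would not meet an outcome defined at near final height, so the definition would still need changing.
- **Follow-up may be longer.** The Fig. 2 legend says so, and the assessments could then still take place. That conflicts with Planned interventions and Planned final analyses, so it supports reconciling the text rather than dismissing the point.
- **Bone age may not matter.** Under the growth-rate definition in Study procedures, a slow-growing child with low bone age is measured. Selection would then be on growth rate alone. And if bone age must be checked to declare near FH, some films may already exist.
- **Bone outcomes are analysed like the primary.** This might be read as carrying over the end-of-study substitute, but no measurement is named that would supply the value.
- **The event is expected to be rare.** No rate contradicts this.

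A reader might go further and infer that bone age delay is truncated on its own value, that the missing children are the most delayed, and that a harmful effect of stopping GH would be hidden. The documents do not support that: the threshold is on absolute bone age, the missing group mixes young and delayed children, and the attenuation figures depend on assumed rates. Nor do the documents say that these children drop out.

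**Conclusion.** The point holds in a limited form. In the text shown, if follow-up closes at 36 months, children not at near FH have no defined bone or lipid follow-up value, and those comparisons are restricted to children selected on post-randomisation growth and, under two of the three definitions, bone maturation. That sits badly with the planned ITT analyses.

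The number affected is unknown: 6 to 23 of 114 under an assumed 5–20%, and the upper end fits poorly with the plan's expectation of rarity. The direction and size of any bias are unknown. The primary outcome, its height substitute and the sample size are unaffected. IGF-1 is less exposed because it is also drawn during follow-up. The conclusion rests on the visible text and would narrow if Fig. 2 or the full protocol schedules these measurements at the last visit.

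**What to change.** 1. Reconcile Planned interventions, the Fig. 2 legend, Study procedures, Missing data and sensitivity analyses, and Planned final analyses on when follow-up ends and on one definition of near FH, including which bone age belongs to which sex.
2. Take the already planned second X-ray and fasting lipids at each child's last visit, whether near FH or end of study, and define the bone and lipid outcomes at that visit for all randomised children. This matches the existing rule for height.
3. Flag values taken before near FH and repeat the bone and lipid analyses without them, parallel to the sensitivity analysis already planned for height.
4. For the stimulation test, only reconcile the sections so that they state what happens in children who do not reach near FH.

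The cost is mainly wording in the schedule and outcome definitions, plus the planned assessments in the few children who would otherwise miss them. Trial status reports no participants recruited at publication, so the change was cheap at that point. The downside is that a few values are taken before growth is complete, so the outcome is no longer purely a near-FH measurement; step 3 shows whether that matters.

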#### Sample size and power calculation

Determination of non-inferiority margin was carefully considered, following extensive consultation. A questionnaire was sent to all investigators, British Society for Paediatric Endocrinology and Diabetes clinical study group members, and a patient support group representative (*n* = 34), giving several options for ‘acceptable deficit’ in various FH outcomes. These FH outcome options for comparison between the GH + and GH − groups were (1) the percentage of children reaching normal adult height (0 ± 2SD), (2) the percentage of children reaching mid-parental TH (0 ± 2SD) and (3) the near FH (in SDS/cm). Near-FH standard deviation score (near FH-SDS) was selected as the primary outcome.

Whilst the percentage of children reaching mid-parental TH [26] was the most popular outcome amongst respondents, data were not available to inform a sample size calculation. However, all the above options to express FH will be analysed in this trial as secondary outcomes. Other secondary outcomes are HRQoL, lipid profile, cost-effectiveness, and the bone health index (assessing effect of GH + /GH − on bone accrual and bone age using BoneXpert software).

For the primary outcome measure of near FH-SDS with a non-inferiority design comparing means and assuming equal variance, a non-inferiority margin of 0.55 near FH-SDS, a one-sided test with alpha = 0.025 and 90% power, a group size of 57 (total *n* = 114) would be needed (calculated using the SSI procedure in Stata 13). This calculation was based on a near FH-SDS (SD) of − 1.6 (0.9) using data from a population-based registry for patients with idiopathic GHD treated with GH and completing the scheduled treatment [27]. The non-inferiority margin is based on clinical opinion. Additional observational studies gave consistent results. Using the LMS growth software, a 0.55 height SDS score (using British 1990 Growth Charts [28]) approximates to 3.8 cm for boys and 3.3 cm for girls at age 23. With 17% allowance for withdrawal and loss to follow-up, a total sample size of 138 is required.

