#### Randomisation

Following confirmation of patient eligibility, receipt of informed consent and completion of all questions and data items on the randomisation form, the patient will be randomised at the level of the individual in a 1:1 ratio to either continue (GH +) or discontinue (GH −) growth hormone therapy. Randomisation will be provided by a secure online randomisation system at Birmingham Clinical Trials Unit (BCTU). A minimisation algorithm will be used within the online randomisation system to ensure balance in the treatment allocation over the following variables:Tanner stage (B2 (females) or 6– < 9 ml testicular volume of the largest testicle (males) vs B3 (females) or 9–12 ml testicular volume (males).Sex (male vs female).Participating centre.

Following randomisation, a confirmatory e-mail will be sent to the responsible clinician including the child’s trial number and treatment allocation.

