### Primary outcome measure

The primary outcome measure is near FH-SDS (using the WHO Growth Charts [29]) and is considered a non-inferiority outcome. The groups will be compared using a linear regression model adjusting for the minimisation variables and baseline height SDS, to compare the mean near FH-SDS between the GH + and GH − group. The adjusted mean difference in near FH-SDS will be presented alongside a 95% confidence interval. Non-inferiority for the primary outcome will only be concluded if the lower bound of the 95% confidence interval limit is above − 0.55 for both the ITT and per-protocol analyses.

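### The 90% power is for one unadjusted comparison on 114 children, but success requires both the ITT and the per-protocol analysis to pass, and the power of that joint rule is not stated

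*Protocol article*

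**What the plan says.** The protocol article, under Sample size and power calculation, plans the primary comparison "with a non-inferiority design comparing means and assuming equal variance", with "a non-inferiority margin of 0.55 near FH-SDS" and "a one-sided test with alpha = 0.025". It combines that alpha with an SD of 0.9 "and 90% power, a group size of 57" per arm, 114 in total. The SD was obtained "using data from a population-based registry for patients with idiopathic GHD treated with GH and completing the scheduled treatment", so it is an unadjusted population figure. The section then applies a 17% "allowance for withdrawal and loss to follow-up, a total sample size of 138 is required".

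Under Primary outcome measure the success rule is: "Non-inferiority for the primary outcome will only be concluded if the lower bound of the 95% confidence interval limit is above" −0.55, and this must hold for both the ITT and the per-protocol analysis. The model there adjusts for the minimisation variables and baseline height SDS.

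Three other places bear on the point:

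- Statistical analysis limits the per-protocol set to adherent participants and leaves the definition to the SAP. No expected exclusion rate is given.
- Missing data and sensitivity analyses leaves children without a primary outcome out of the primary analysis.
- Study procedures has a hand X-ray at enrolment, and Secondary outcomes needs target height. Neither bone age nor target height is in the primary model.

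**The concern.** When two analyses must both succeed, the chance of success cannot exceed that of the weaker one. Here the weaker one is per-protocol, which is a subset of the ITT set. The 17% allowance is used up in getting from 138 randomised to 114 with an outcome, so any further exclusion for non-adherence takes the per-protocol set below the 114 on which the 90% rests.

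Such exclusions are foreseeable. The GH+ arm faces up to about three years of daily injections in an open-label trial. Some GH− children may restart treatment after a low IGF-1 at 6 months, and the SAP may or may not count them as adherent.

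What is at stake is the risk of failing to show non-inferiority when it is true. False claims of non-inferiority are not the issue, because requiring both analyses is the more cautious rule.

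**Working it through.** **Inputs.** Margin 0.55, SD 0.9 in each arm, one-sided alpha 0.025, power 90% and attrition 17% come from Sample size and power calculation. Allocation is "randomised at the level of the individual in a 1:1 ratio" (Randomisation). The true difference is taken as 0; the article does not state it, but 57 per arm needs it. The per-protocol exclusion share e, among children with an outcome, is my assumption and is shown over a range.

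**1. Reproduce the plan's figures.**

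n per arm = 2 × 0.9² × (1.960 + 1.2816)² / 0.55² = 56.27, rounded up to 57. Total 114.

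114 / 0.83 = 137.3, rounded up to 138.

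The plan's figures reproduce. Power at 57 per arm: 0.55 / (0.9 × √(2/57)) − 1.960 = 1.302, which gives 90.4% (89.9% with the noncentral t). There is almost no slack.

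**2. Joint power with no covariate gain.** The per-protocol set has 57 × (1 − e) per arm. If exclusions are unrelated to outcome, the two estimates are nested and correlate at √(1 − e). Joint power is the bivariate normal probability that both lower limits clear −0.55. At e = 10%, for example, per-protocol n is 51.3 per arm, and 0.55 / (0.9 × √(2/51.3)) − 1.960 = 1.135, or 87.2%. Combined with 90.4% for ITT at correlation 0.949, joint power is 86.0%.

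| e | Per-protocol n per arm | Per-protocol power | Joint power |
|---|---|---|---|
| 5% | 54.2 | 88.9% | 87.9% |
| 10% | 51.3 | 87.2% | 86.0% |
| 15% | 48.5 | 85.3% | 84.0% |
| 20% | 45.6 | 83.1% | 81.8% |
| 30% | 39.9 | 77.9% | 76.7% |

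**3. Allow for covariates.** If the covariates in the model together explain a share R² of the variance, the SD becomes 0.9 × √(1 − R²): 0.854, 0.805 and 0.753 at R² = 0.1, 0.2 and 0.3. Joint power is then:

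| R² | e = 10% | e = 15% | e = 20% | e = 30% |
|---|---|---|---|---|
| 0 | 86.0% | 84.0% | 81.8% | 76.7% |
| 0.1 | 89.5% | 87.8% | 85.8% | 81.1% |
| 0.2 | 92.7% | 91.3% | 89.7% | 85.6% |
| 0.3 | 95.5% | 94.5% | 93.3% | 90.0% |

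Total R² needed for joint power of 90% is about 0.07, 0.12, 0.16, 0.21 and 0.30 at e = 5, 10, 15, 20 and 30%. The corresponding correlations with near FH-SDS are 0.26, 0.34, 0.40, 0.46 and 0.55.

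**4. Allow for lower attrition.** With 138 randomised and no covariate gain, 5% attrition gives joint power of 90.5% at e = 10% and 87.0% at e = 20%. With no attrition it is 91.9% and 88.7%.

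**The case against.** The strongest reply is that the power figures without covariate gain describe an analysis the trial will not run. The primary model already includes baseline height SDS, sex, Tanner stage and centre, and the sample size takes no credit for them. A correlation of about 0.34 with near FH-SDS would offset 10% exclusions, and about 0.46 would offset 20%. This stands. A reader might infer that the stated power is not delivered, but the documents do not support that, because they give neither the correlation nor an exclusion rate.

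The calculation also takes the full 17% attrition and then removes different children for non-adherence. Withdrawal is not defined, so the two groups may overlap. Missing data are expected to be minimal, and eligibility screens for ability to comply. This stands too, and step 4 shows its effect.

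The per-protocol definition belongs to the SAP. That is so, and its absence here is no fault. But the article itself states both a power figure and a decision rule, and the figure is for a different rule.

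Finally, a reader might infer that bone age and target height would make good the loss. That cannot be shown: their gain beyond baseline height SDS, sex and Tanner stage cannot be computed from the documents, and the planned covariates may already be enough.

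**Conclusion.** The concern holds as a mismatch between the power statement and the decision rule. It is not an arithmetic error, since 57, 114 and 138 are all correct for the single test they describe.

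Before any covariate gain and with the full 17% attrition, joint power is about 2 to 9 points below 90.4% for exclusions of 5% to 20%. At 20%, the chance of missing true non-inferiority rises from about 10% to about 18%. Covariates or lower attrition could remove this shortfall or more than remove it, so whether the trial has less than 90% power is open.

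The figures rest on a true difference of 0, a common SD of 0.9, and exclusions unrelated to outcome. The first matters most: a true deficit of 0.10 SDS would by itself bring single-test power down to 76.1%.

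**What to change.** Two changes, neither of which alters enrolment:

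1. In Sample size and power calculation, keep 57 and 138 but report the power of the joint ITT and per-protocol rule. State the assumed per-protocol exclusion rate and the assumed total R² of the planned model, and show the range, for example as in the second table above.
2. Pre-specify enrolment bone age (or bone age minus chronological age) and target height SDS as further covariates in the primary model, beside baseline height SDS. At similar Tanner stages, height SDS for age mixes stature with the tempo of maturation, so some added precision is reasonable to expect. Do not claim a size for it without data.

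The cost is a reworded paragraph, two lines in the SAP, and simple imputation of any missing covariate values. The headline power may look less favourable under some assumptions. The article reports that no children had been recruited at publication, so at that point both changes could be made before any outcome data existed.
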